### Description of the standard of care

Currently the standard of care for RMNCH at the community level in both districts of the study is the care delivered by FCHVs. FCHVs are women selected by mother’s groups in each of the villages and serve in a voluntary capacity, receiving some financial incentives but no salary. After an initial 18-day training, they receive a certificate and a medical kit including basic medications, such as iron and folate tablets for pregnancy and oral rehydration salts for diarrheal diseases. They have short training sessions when new programs are added to their workload and have minimal ongoing training. FCHVs are minimally supervised by the government village clinic staff, and they do not use mobile tools in a widespread fashion [45, 46]. They are engaged in health promotion, distribution of preventive health commodities (such as iron-folate tablets and family planning methods), and home health care provision, using CB-IMNCI algorithms to diagnose and treat childhood illnesses and make referrals when needed [12]. There may be other non-governmental programs operating in Achham and Dolakha working with local FCHVs and health care facilities. We will take note of these programs and the services they are providing to understand how our results may be affected.

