Through a public-private partnership in rural Nepal between the Ministry of Health and the healthcare delivery organization *Possible*, we built an integrated CHW intervention that employs full-time, salaried CHWs to deliver evidence-based interventions to improve maternal, newborn, and child health outcomes (see Additional file 1 for a detailed description of the intervention and Additional file 2: Figure S1 for the management structure). *Possible* has found that as rural Nepal has improved education access and retention for girls, there is a sufficient talent pool for hiring local women with a 10th grade education and higher as CHWs. Additionally, rural Nepal has rapidly become technologically connected though mobile phones and cellular data and, like many low- and middle-income countries, can take advantage of mobile applications for health.

*Possible’s* CHWs deliver community-based care facilitated by use of mobile technology [16]. CHWs monitor and promote utilization of services; provide maternal and neonatal health counseling; promote self-efficacy, social support, and emergency planning; and diagnose and refer for major causes of RMNCH morbidity. The evidence-based intervention they deliver is comprised of five integrated components: (1) home-based antenatal care (ANC) and postnatal (PNC) counseling and care coordination; (2) continuous surveillance of all reproductive age women, pregnancies, and children under age two via an integrated electronic health record system; (3) Community-Based Integrated Management of Neonatal and Childhood Illness (CB-IMNCI); (4) group ANC and PNC; and (5) the Balanced Counseling Strategy to post-partum contraception.

We have previously assessed this integrated intervention over an 18-month time-period in a geography covering a population of 33,000. The evaluation demonstrated an increase in key service utilization: institutional birth, ANC visit completion, and use of modern contraceptive methods in the postpartum period. This evaluation was conducted as a pre-post assessment, and several components of the intervention were actively being rolled out during and after the intervention period [17]. The data, however, were encouraging and call for a more rigorous evaluation at scale.

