### Study site

The study will take place in Achham and Dolakha districts of Nepal. The intervention will be implemented in step-wise fashion across the village clusters in coordination with district authorities and study staff.

Achham is located in the hilly far western region of Nepal, home to the highest under-five mortality rates in the country at 82 (one in 12) deaths per 1000 live births [43]. This region has suffered the consequences of war, long-standing poverty, and a concentrated HIV epidemic. *Possible* implements community health care delivery programs and independently manages the government-owned district-level Bayalpata Hospital, a 50-bed facility that serves approximately 80,000 outpatients and 2000 inpatients per year. CHW services in Achham will be expanded to 40 village clusters with approximately 200,000 people.

The second location will be in Dolakha district, one of the hardest hit districts and the epicenter of the second earthquake in 2015 [44]. Upon invitation by the Ministry of Health, *Possible* began managing Charikot Hospital in Dolakha in January 2016. Charikot Hospital is a 35+ bed facility that treats approximately 50,000 outpatients each year. The intervention will be scaled up district-wide during the course of the study. Forty village clusters with approximately 100,000 people will be included.

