### Study population

The study population will include women of reproductive age (between ages 15–49) and children from 0 to 24 months of age enrolled in continuous surveillance, home-based care, and/or monthly group ANC led by *Possible’s* team in Achham and Dolakha. Specifically, this will include patients receiving health care services at Bayalpata Hospital in Achham and Charikot Hospital in Dolakha or household-level care through networks of CHWs across both districts.

Staff members involved in the program will be approached for key informant interviews (KIIs) and focus group discussions (FGDs). For all qualitative methods, we will use purposive sampling aiming to maximize heterogeneity across sex, socioeconomic position, health care issues, geographic location, age, caste-class, and other attributes. KIIs will be conducted with participants of the group ANC groups, recently delivered women, women receiving antepartum and postnatal home-based care, and reproductive age women receiving pregnancy screening. KIIs will also be conducted with team members who implemented the interventions, community leaders, and government leaders.

Participants eligible for inclusion in the study include the following: (1) married, reproductive-aged women 15–49; (2) reproductive-aged women 15–49; recently delivered in past 2 years; (3) reproductive-aged women 15–49 with active pregnancy during study period and identified by a CHW serving their village; (4) children aged 0–2 of recently delivered mothers (population 2 or 3 above); and (5) health care staff members including CHWs serving village clusters, research performance site employees involved in study design, program implementation, data collection, or data analysis processes. Study populations 1–4 must reside in either Achham or Dolakha.

Individuals meeting inclusion criteria, as stated above, will be included in the study without exclusion unless (1) individuals migrate from the study before completion of any of the integrated interventions or (2) individuals explicitly request exclusion from the study and decline to consent to the study.

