### Study design

This is a type 2 hybrid effectiveness-implementation research study examining an integrated RMNCH intervention. This intervention integrates the five evidence-based approaches described above, focused on the “golden 1000 days” from conception through age two. We plan to study the impact on population health outcomes using a pre-post quasi-experimental design with stepped implementation as it is rolled out by CHWs in Achham and Dolakha. We will assess the implementation process using the RE-AIM framework, closely examining reach, efficacy, adoption, implementation, and maintenance.

We will evaluate the intervention as it is rolled out in stepped implementation. Implementation will occur in sub-populations of about 20,000 at a time (including village clusters of 1000 to 6000 people). Full implementation of the integrated intervention in any sub-population will take 6 months. Approximately 80 clusters across the two sites will be involved in the study, with a total population of approximately 300,000. This is incorporated into the power calculations below.

In this pragmatic trial, village cluster units are determined by Nepal administrative boundaries. Enrollment and timing of enrollment are based upon local government decision-making and as such cannot be randomized. Data collection is developed and integrated within the routine course of care, because this is the approach we have found to be ethical, acceptable, and affordable in our context. This has the following implications: (1) the number of villages per cluster is variable, (2) interval between new clusters being ramped up can be variable from the scheduled start times, and (3) baseline data occurs at the beginning of each step rather than at study start.

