		Maintenance cost	% breakdown of maintenance costs (personnel, materials, and other)
		Facility vs. community costs	% of costs of health care divided between facility level and community level
		Geographic cost variation	Variation of costs between village clusters and districts
		Out-of-pocket patient costs	% costs of health care divided between facility level and community level
		Integrated intervention cost-effectiveness	Pre/post intervention marginal effectiveness for primary outcomes, not account for secondary effects (e.g., increasing the costs of care through increased cesarean sections)

The primary predictor is the effect of the intervention measured in 3-month intervals throughout the study period, comparing to the FCHV standard-of-care control at baseline. Calendar month will be included as a separate covariate to control for the overall secular trend. Variables will be considered as both nominal and continuous (linear effect) predictors, and the generalized linear model framework will be used to estimate effect of time-varying repeated measure intervention implementation over the several steps of the wedged design. Differential impact from time of intervention will be evaluated with test of month × intervention interaction. Models will be fit using generalized estimating equations, e.g., using SAS Proc Genmod, to calculate valid standard errors in the presence of repeated measures over time and possibly correlated outcomes at the village cluster level. Assumptions of over- or under-dispersion will be examined closely, and an estimated scale parameter or negative binomial models will be used as needed.

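### The Aim 1 control is taken to be FCHV care everywhere, yet CHW services already operate and no rule keeps previously served clusters out of that control

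*Protocol article*

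**What the plan says.** All references are to the protocol article.

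**The comparator.** Under Description of the standard of care, the article states: "Currently the standard of care for RMNCH at the community level in both districts of the study is the care delivered by FCHVs". The statement carries no exception for areas where the implementing organisation already works. The Aim 1 analysis builds its main predictor by "comparing to the FCHV standard-of-care control at baseline".

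**Earlier CHW activity.**
- Background: "We have previously assessed this integrated intervention over an 18-month time-period in a geography covering a population of 33,000". It adds that "several components of the intervention were actively being rolled out during and after the intervention period".
- Evidence for the integrated intervention: a salaried CHW cadre was recruited and trained. Pregnancy surveillance, group care and postpartum contraception counselling were then added. Group antenatal care had a cluster-controlled trial of its own in rural Nepal.
- Study site: "CHW services in Achham will be expanded to 40 village clusters with approximately 200,000 people". For Dolakha: "Forty village clusters with approximately 100,000 people will be included".

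**Who enters, and when baseline is taken.**
- Sample size describes a census of the catchment.
- Study population says that eligible people "will be included in the study without exclusion unless" they move away or decline.
- Study design: "baseline data occurs at the beginning of each step rather than at study start". Data collection ties baseline to the start of the intervention in each cluster, and the Discussion places it just before each step is implemented.

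**The concern.** The comparator statement and the history of the programme do not fit together. If CHW services in Achham are to be expanded to 40 clusters, some already exist there, and the natural reading is that the 40 include the places already served. In such a cluster the study step begins after CHWs arrived. Data collected at that point describe CHW care, in whole or in part, but the Aim 1 definition would label them FCHV control.

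Two things follow for any such cluster. Its before-after contrast sets CHW care against CHW care, which pulls the pooled estimates for all three Aim 1 outcomes toward no effect. The conclusion about CHW versus FCHV care also does not apply to that part of the population. This matters because the Background says the findings are to inform a new government CHW system.

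**Working it through.** **1. Passages side by side.** The standard-of-care section and the Aim 1 analysis allow one baseline condition, FCHV care. The Background, Evidence and Study site sections describe a second, CHW care already being delivered. The only exclusions listed are migration and refusal, and both apply to individuals. Nothing states how a previously served cluster is treated. For such a cluster the text also does not say whether the baseline date is the study step or the earlier arrival of CHWs.

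**2. The protocol's own totals.**
- Population: 200,000 + 100,000 = 300,000, as stated.
- Deliveries: 8,000 per year × 1.5 years = 12,000, as stated.

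No stated figure deals with earlier exposure.

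**3. Size of the attenuation, if overlap exists.** Let *s* be the share of the study population previously served, and *f* the fraction of the effect already present there at baseline. If clusters count in proportion to their births, and births follow population, then

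observed effect = true effect × (1 − *s* × *f*).

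The 33,000 is the only figure given for earlier coverage, so the largest *s* is 33,000 / 300,000 = 0.11. The 15% hypothesis for institutional birth is not stated to be absolute or relative. The table takes it as 15 percentage points.

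| Assumption | *s* × *f* | Observed effect |
|---|---|---|
| No previously served cluster in the study | 0 | 15.0 points |
| All 33,000 in the study, half the effect present | 0.055 | 15 × 0.945 = 14.2 points |
| All 33,000 in the study, full effect present | 0.11 | 15 × 0.89 = 13.35 points |

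If the 15% is relative and the FCHV-level rate is the same in all clusters, the bottom row becomes a rate ratio of 1.15 / (1 + 0.11 × 0.15) = 1.15 / 1.0165 = 1.13.

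At the same upper bound the secondary hypotheses shrink from 10 to 8.9 (10 × 0.89, contraception, read as points) and from 2 to 1.78 deaths per 1,000 (2 × 0.89).

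**4. Births involved.** At most 8,000 × 0.11 = 880 per year, or 12,000 × 0.11 = 1,320 over 18 months.

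**5. Power.** An illustrative two-proportion calculation used 6,000 deliveries before and 6,000 after, each divided by the design effect. No baseline rate is given for the study population, so values from 30% to 77% were assumed, the range reported in the earlier facility survey.
- A 15-point rise: power stays near 100% with or without the 11% dilution, at design effects of 1.8 (the stated maximum) and 2.0.
- A 15% relative rise from 30%, the weakest case at these design effects: power goes from 97.6% to 93.7% at 1.8, and from 96.2% to 91.2% at 2.0.

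**The case against.** The strongest reply is that overlap is not shown. The Background does not name the district of the 33,000. The Evidence section places the group antenatal care trial only in rural Nepal. The sentence about expansion could mean that the 40 clusters are new ground. This stands: a reader might infer that pilot clusters are certainly in the study and the effect certainly diluted, and the documents do not go that far.

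A second reply is that baseline is taken just before implementation, so it precedes the intervention by definition. This helps only if the reference date is the cluster's first CHW contact. The text ties baseline to the study step, which in a served cluster comes later. Going back to the earlier date would bring in data from before the study, while the Discussion prefers step-specific baselines to historical controls.

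A third reply is that an article may leave the cluster list to a fuller document. That is fair for the list itself. The unqualified comparator statement is in this article, however, and conflicts with other parts of it. The promise to note other non-governmental programmes, and the limitation about them in the Discussion, do not mention the implementer's own earlier services.

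A reader might also expect served clusters to enter first and so distort the adjustment for secular trend. No roll-out order is given, and timing is left to local government, so this is conjecture. Nor is there support for quoting a larger loss for Achham alone, because no district-specific estimate is stated.

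**Conclusion.** The concern holds in conditional form. The article states an FCHV-only baseline although CHW services delivering the same components already operate, and it gives no rule for clusters served before their step. If any are among the 80, part of the control is the intervention and the estimated effect is attenuated.

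The loss runs from zero to at most 11% of the effect. The upper end needs all 33,000 to be inside the study clusters, fully exposed at baseline and coded as control. It also takes 33,000 as the whole earlier coverage and weights clusters by births. Full exposure is unlikely, since several components were still being introduced during and after the earlier evaluation.

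Power is not the issue at design effects near the one stated. What matters is a biased estimate and a wrong label on the comparison, and more births would cure neither.

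**What to change.** 1. In Description of the standard of care, limit the FCHV statement to clusters without earlier CHW services.
2. Flag each of the 80 clusters for earlier CHW services or any of the five components, including clusters from the 18-month evaluation and the group antenatal care trial, with the true start date.
3. In the Aim 1 analysis, state that step-start data from flagged clusters are never coded as FCHV control. Exclude these clusters from the primary Aim 1 contrast.
4. Add a sensitivity analysis that includes them, coded as exposed from their true start date.
5. Keep them in the Aim 2 RE-AIM analysis.
6. If no study cluster was previously served, say so. Steps 2 to 5 then fall away.

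The cost is a few sentences and one cluster-level variable that the implementing organisation should be able to supply. The downside is at most about 11% fewer births in the primary contrast (about 880 of 8,000 a year), from clusters whose step-start data were not a clean FCHV baseline.

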### Study design

This is a type 2 hybrid effectiveness-implementation research study examining an integrated RMNCH intervention. This intervention integrates the five evidence-based approaches described above, focused on the “golden 1000 days” from conception through age two. We plan to study the impact on population health outcomes using a pre-post quasi-experimental design with stepped implementation as it is rolled out by CHWs in Achham and Dolakha. We will assess the implementation process using the RE-AIM framework, closely examining reach, efficacy, adoption, implementation, and maintenance.

We will evaluate the intervention as it is rolled out in stepped implementation. Implementation will occur in sub-populations of about 20,000 at a time (including village clusters of 1000 to 6000 people). Full implementation of the integrated intervention in any sub-population will take 6 months. Approximately 80 clusters across the two sites will be involved in the study, with a total population of approximately 300,000. This is incorporated into the power calculations below.

In this pragmatic trial, village cluster units are determined by Nepal administrative boundaries. Enrollment and timing of enrollment are based upon local government decision-making and as such cannot be randomized. Data collection is developed and integrated within the routine course of care, because this is the approach we have found to be ethical, acceptable, and affordable in our context. This has the following implications: (1) the number of villages per cluster is variable, (2) interval between new clusters being ramped up can be variable from the scheduled start times, and (3) baseline data occurs at the beginning of each step rather than at study start.

### Sample size

This implementation research study uses a census methodology rather than a representative sample. The programmatic intervention aims to reach all individuals within the catchment area population given the research performance site’s care mandate to serve this population. All individuals in the catchment area population, as defined under study site above, who meet the inclusion criteria will be approached for inclusion into the programmatic intervention, for which their de-identified clinical data will be analyzed towards the primary aim. The sample size is determined by the overall population covered in the two districts of 300,000, (rather than calculated via a sample size formula) within which we anticipate approximately 8000 deliveries per year or 12,000 during the first 18 months of the study during which enrollment will occur.

To calculate power for the primary outcome of institutional birth rate, we consider a Poisson regression model with 0.05 significance level and two-sided power of 80 or 90%. We further assume a 1-year exposure mean per child over the course of the intervention. We will consider models where the secular trend and other covariates explain 25 or 50% of the total variance in mortality. We assume intra-cluster correlation of outcomes would range from 0.2 to 0.8 for design considerations. Based on these parameters and recent advances in stepped wedge methodology [47], we calculated a design effect ranging from 0.3 to 0.8 to account for the wedge design. To be conservative, we further included a multiplicative design effect of 2.5 to account for cluster randomization, resulting in an overall design effect of 1.8 at a maximum.

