### Data analysis

#### Analysis for specific Aim 1: effectiveness

For assessing effectiveness, we focus on three population health outcomes as shown in Table 1. We hypothesize the integrated intervention will lead to a 15% increase in the institutional birth rate—Primary Outcome 1—among reproductive age women in the study population over the three-year study period. We hypothesize the integrated intervention will lead to a two death per 1000 reduction in the under-two mortality rate—Secondary Outcome 1—in the study population over the three-year study period. We hypothesize the integrated intervention will lead to a 10% increase in modern PPCPR—Secondary Outcome 2—among recently delivered women (defined as having had a live birth in the preceding 24 months) in the study population over the three-year study period.

**Table 1 Tab1:** Evaluation framework

Aim	Outcome/RE-AIM element	Indicator	Definition
Effectiveness	Primary outcome 1: institutional birth	Institutional birth rate	% women delivering at a facility with a skilled birth attendant
	Secondary outcome 1: child mortality	Under-2 mortality rate	# child deaths before age 2 per 1000 live births
	Secondary outcome 2: post-partum contraception	Post-partum contraceptive prevalence rate	% post-partum women using a modern form of contraception
Implementation	Reach	Home visit coverage	-% children under age 2 years receiving a CHW home visit, measured monthly -% pregnant women receiving a home visit by a CHW, measured monthly -% reproductive aged women receiving a pregnancy surveillance home visit, measured quarterly -% postpartum women receiving 1+ balanced counseling session, measured biannually
		Group participation	% scheduled participants completing group sessions, measured monthly
		Session completion	% scheduled group sessions completed, measured monthly
		Demographic, geographic barriers and facilitators	Mapping households, describing barriers/facilitators to individuals’ access, and identifying contributors to variation/inequities
	Efficacy	Pregnancy identification	% all pregnancies identified in first 12 weeks
		ANC completion	-% women at 9+ months gestation completing 4+ ANC visits at a health care facility and eligible for government financial incentive out of total # of women delivered, measured monthly -% pregnant women who receive an obstetric ultrasound by their due date, measured monthly -% pregnant women with prenatal labs completed by 6 months gestation, measured monthly

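### The power paragraph for institutional birth is built on under-two mortality inputs, so the stated 80 or 90% has no valid basis for the primary outcome as written

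*Protocol article*

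**What the plan says.** The Sample size section first explains that the study is a census of a population of about 300,000. It expects about 8,000 deliveries a year, or 12,000 in the first 18 months, and says the size was not set by a formula. It then gives a power calculation anyway:

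- Label and model: "To calculate power for the primary outcome of institutional birth rate, we consider a Poisson regression model with 0.05 significance level", with the power set at 80 or 90%.
- Exposure: "We further assume a 1-year exposure mean per child over the course of the intervention".
- Explained variance: "We will consider models where the secular trend and other covariates explain 25 or 50% of the total variance in mortality".
- Clustering: "We assume intra-cluster correlation of outcomes would range from 0.2 to 0.8 for design considerations". A stepped-wedge factor of 0.3 to 0.8 and a cluster factor of 2.5 follow, with an overall maximum given as 1.8.

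The paragraph stops at that design effect.

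The hypothesised effects stand elsewhere, under Analysis for specific Aim 1. They include a 15% increase in institutional birth (primary) and, for secondary outcome 1, "We hypothesize the integrated intervention will lead to a two death per 1000 reduction in the under-two mortality rate". Table 1 defines institutional birth as the percentage of women who deliver in a facility with a skilled attendant, and under-two mortality as deaths per 1000 live births.

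**The concern.** Institutional birth is one yes/no result per delivery. It has no follow-up time per child, and the variance in mortality that covariates explain says nothing about it. Both inputs fit under-two mortality. The paragraph thus names one outcome and parameterises another, and nothing else in the article reconciles the two.

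Two things are at stake. A reader will take the study to have 80 or 90% power for its primary outcome, although the stated inputs cannot yield that figure for it. A reader who notices the mortality inputs may instead carry the 80 or 90% over to the mortality hypothesis, and then read a null mortality result as evidence of no effect. The study is described as a national pilot meant to inform policy, so that misreading would matter.

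**Working it through.** **1. Can the stated figure be reproduced?** No. The 80 or 90% is a chosen level. No baseline institutional birth rate and no effect size enter the paragraph, so there is nothing to compute it from. Of the paragraph's own arithmetic:

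- Deliveries: 8,000 × 1.5 = 12,000, which agrees.
- Overall design effect: 0.3 × 2.5 = 0.75 at the lowest and 0.8 × 2.5 = 2.0 at the highest. The stated maximum is 1.8, which would need a wedge factor of 1.8 / 2.5 = 0.72.

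**2. What would the same deliveries give for institutional birth?** Assumptions: 12,000 deliveries split 6,000 before and 6,000 after, two-sided 0.05, 80% power, and a baseline of 30 to 77%. The study baseline is not stated; 30 and 77% are the two levels quoted from the earlier survey.

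Detectable difference = (1.960 + 0.842) × √(2p(1−p) × DE / 6,000)

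| Baseline p | DE 1.8 | DE 2.0 |
|---|---|---|
| 0.30 | 3.1 points | 3.3 points |
| 0.50 | 3.4 points | 3.6 points |
| 0.77 | 2.9 points | 3.0 points |

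If the 15% is relative, the smallest absolute change in this range is 0.15 × 30 = 4.5 points, at a baseline of 30%. Power there is 97.6% at DE 1.8 and 96.2% at DE 2.0. For a rise of 15 points, power exceeds 99.9% throughout.

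**3. Does the 80 or 90% hold if it was really derived for mortality?** Assumptions: a reduction of 2 per 1000, equal split, and an under-two baseline of 10 to 82 per 1000. The article gives no under-two rate. The 82 is the under-five rate it cites for the far western region.

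SE = √(DE × (1−R²) × (p₁q₁ + p₂q₂) / n per period), where q = 1 − p and R² is the share of variance removed

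Power = Φ(0.002/SE − 1.96) + Φ(−0.002/SE − 1.96)

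With 12,000 births, DE 1.8 and no variance removed:

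- 10 per 1000: SE = √(1.8 × (0.0099 + 0.007936) / 6,000) = 0.00231; power 13.9%.
- 82 per 1000: SE = √(1.8 × (0.075276 + 0.0736) / 6,000) = 0.00668; power 6.0%.

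Most generous case: 24,000 births (8,000 × 3 years), DE 0.75, and the stated 50% of variance removed:

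- 10 per 1000: SE = √(0.75 × 0.5 × 0.017836 / 12,000) = 0.00075; power 76%.
- 20 per 1000: power 46%.
- 30 per 1000: power 33%.
- 82 per 1000: SE = √(0.75 × 0.5 × 0.148876 / 12,000) = 0.00216; power 15%.

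A Poisson log-rate-ratio version of this case gives nearly the same figures (75.8% at 10 and 45.0% at 20 per 1000). No tested scenario reaches 80%.

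**The case against.** Several points on the other side stand.

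- **Poisson regression is not the error.** A log-link Poisson model with GEE standard errors is a recognised way to analyse a binary outcome, and the analysis section provides for GEE and a scale parameter. Poisson variance p in place of p(1−p) would make the calculation conservative. The fault lies in the child-exposure and mortality-variance inputs.
- **The sample is a census.** No enrolment decision depends on the paragraph. That limits the harm, but a power calculation that is presented should describe the outcome it names.
- **An article condenses.** A baseline rate or a detectable difference may stand in the full protocol, and their absence alone would be no finding. Inputs for the wrong outcome are a misstatement in the text shown.

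Two stronger readings are tempting, and the article supports neither.

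- A reader might infer that the study claims 80 or 90% power for mortality. It does not: the figure is attached only to institutional birth, and mortality is a secondary outcome with a hypothesised effect and no power claim. A protocol need not power each secondary outcome.
- A reader might infer that the primary outcome is underpowered. At the stated design effect the deliveries are ample. It is true that a plain parallel-cluster formula with 12,000 / 80 = 150 births per cluster and the stated correlation gives 1 + 149 × 0.2 = 30.8 to 1 + 149 × 0.8 = 120.2, with power from about 7% to 98% over baselines of 30 to 77%. That formula ignores the within-cluster comparison of a stepped design, so it is a sensitivity range and not evidence of a shortfall.

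**Conclusion.** The concern holds as a misparameterised power statement. The paragraph is labelled for institutional birth, uses under-two mortality inputs, and leaves out the 15% effect. As written, the 80 or 90% has no valid basis for the primary outcome. The wrong inputs and the 2.0 versus 1.8 mismatch can be read directly from the article and need no assumption.

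The consequence for the primary outcome is small if the design effect of 1.8 to 2.0 is accepted, because the detectable difference is then well inside a 15% rise on either reading of that figure. This rests on an equal split and the assumed baseline range.

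The mortality result is conditional. Only if the 80 or 90% was in fact derived for mortality does it fail, and then it fails across the whole assumed baseline range. Whatever its origin, this design is unlikely to detect a reduction of 2 per 1000, and a null mortality result would not show absence of effect.

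The text should be corrected, but this is not a defect that must be resolved before the study can proceed.

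**What to change.** 1. Redo the calculation for institutional birth with the delivery as the unit, using a binomial model or Poisson with robust variance. Remove the child-exposure and mortality-variance inputs.
2. State the assumed baseline rate, whether 15% is absolute or relative, the split of deliveries before and after the start in each cluster, the design effect and the detectable difference. Correct the maximum design effect to 2.0, or give the wedge factor that yields 1.8.
3. For under-two mortality, state its own detectable difference and present the result as an estimate with a confidence interval. Say that a null result will not be read as no effect.

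The cost is one recalculation and some rewording in the Sample size and Aim 1 sections. No further participants or data are needed. The mortality hypothesis will read less favourably.
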